## Results

The first participant was enrolled in May 2023. As of April 2025, 32 patients and 9 controls have been recruited. A second study center opened at Münster University Hospital in December 2024, and more centers may be added, aiming to complete enrollment by December 2026. Follow-up will continue until December 2028, with final results of the observational study expected in 2028. Additional translational projects involving biomaterials are planned, and their study protocols are currently under development.

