## Methods

This study is a prospective, multicenter observational study. The study was approved by the local Ethics Committee (approval no. 22-10501-BO). In preparing this manuscript, we have used the Strengthening the Reporting of Observational Studies in Epidemiology (STROBE) Statement Checklist as a guide (see supplementary material). The study is conducted in accordance with the Declaration of Helsinki and national regulations.

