### Study cohort

The study will enroll 128 participants (64 glioblastoma patients and 64 controls). Glioblastoma patients will be stratified at their first visit after radiotherapy based on extent of resection, MGMT promoter methylation status, initial olfactory test results, MRI findings of olfactory tract involvement, age, and KPS. This approach ensures balanced distribution between normosmia and hyposmia groups. Patients who cannot be assigned to either group will be excluded from further participation. Stratification will occur once post-radiochemotherapy MRI results are available, typically at visit 1 (see Table 1). The controls should essentially match the age and gender of the patients.

**Table 1 Tab1:** Overview of the planned study visits and their contents

	Screening	Baseline	Visit 1	Visit 2	Visit 3	Visit 4	Follow up visits
Signing Informed consent	x						
Verfication of inclusion and exclusion criteria	x	x					
Stratification			x				
Medical history (including cold symptoms)	x	x	x	x	x	x	x
Physical exam		x	x	x	x	x	x
Karnofsky Performance Status Scale	x	x	x	x	x	x	x
Evaluation of progression and survival data		x	x	x	x	x	x
QoL: EORTC QLQ-C30 and EORTC QLQ-BN20		x	x	x	x	x	x
Recording (severe) adverse events grade III/IV according to CTCAE V5.0		x	x	x	x	x	x
Neurocognitive testing (+ Minimal Mental Status Test)		x	x		x	x	x
Laboratory tests		x	x	x	x	x	x
Olfactory testing	x	x	x	x	x	x	x
MRI	x		x	x	x	x	x
FET PET MRI (if indicated in clinical routine)	x	x	x	x	x	x	x
Laboratory tests for scientific purposes (Biobank)		x	x	x	x	x	x
Next Generation Sequencing (if indicated in clincal routine)	x	x	x	x	x	x	x
Testing for aphasia	x						
Psychosomatic testing	x	x	x	x	x	x	x

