#### Sample size calculation and sampling strategy

The sample size was determined for a time-to-event analysis of Overall Survival (OS) using a Cox proportional hazards model. The calculation was based on the primary comparison between glioblastoma patients with hyposmia (defined as'cases'for the calculation) and those with normosmia (defined as'controls'). A hazard ratio (HR) of 0.43 for normosmia vs. hyposmia was used, a value derived from the multivariate analysis for OS in a specific subgroup of patients in the preceding pilot study [12]. As per the pre-specified statistical plan for this prospective trial, event rates over a two-year duration were prospectively defined at 47% for the hyposmia group and 53% for the normosmia group. With a significance level set at 5% and a statistical power of 80%, a total of 128 participants (64 glioblastoma patients and 64 healthy controls) is required to test this hypothesis. To control for key prognostic factors, patients are stratified after enrollment (at Visit 1) based on MGMT promoter methylation, KPS, age, extent of resection and MRI findings of olfactory tract infiltration. These variables, along with olfactory function, will be included as covariates in the final multivariate Cox proportional hazards model to adjust for potential confounding and assess the independent prognostic value of olfaction.

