### Statistics

A Cox proportional hazards regression model will be used to describe the event, overall survival, where the variables MGMT, KPS, age, MRI findings of olfactory tract involvement and olfactory function will be used as the covariates. All models will be check for proportionality and the log likelihood will be used as the criteria for model selection. All statistical analysis and graphics will be conducted in R version 3.5.0 (Boston, MA).

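### Controls are matched on age and gender only and most are still to be enrolled, so the patient-control smell comparison is exposed to centre and period differences

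*Protocol article*

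**What the plan says.** The Methods section states: "This study is a prospective, multicenter observational study".

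On control selection, the Study cohort section says: "The controls should essentially match the age and gender of the patients". Neither centre nor time of testing is mentioned.

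On recruitment, the Results section says: "The first participant was enrolled in May 2023". It then reports: "As of April 2025, 32 patients and 9 controls have been recruited". A second centre opened in December 2024, and "more centers may be added, aiming to complete enrollment by December 2026". The Perspective section gives the healthy controls their purpose: to supply normal values and to tell loss specific to the disease from loss that comes with age.

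For the primary analysis, the Statistics section names a Cox model for overall survival and gives its terms: "where the variables MGMT, KPS, age, MRI findings of olfactory tract involvement and olfactory function will be used as the covariates". The sample size section describes stratification "based on MGMT promoter methylation, KPS, age, extent of resection and MRI findings of olfactory tract infiltration" and enters the same variables, with olfactory function, in the final Cox model. The two lists differ on extent of resection. Neither contains centre.

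**The concern.** Two comparisons of smell are planned, and centre bears on them differently.

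The first is patients against healthy controls. If controls are tested mainly later than patients, or mainly elsewhere, any difference in test administration between centres or over time enters the comparison as though it were an effect of disease. Age and gender matching does nothing against this. It is also a matter of conduct: once a control has been enrolled and tested, an analysis plan can adjust for place and date but cannot change them.

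The second is hyposmia against normosmia among patients, for overall survival. If the share of hyposmic patients and the survival both differ by centre after the planned adjustment, a model without centre attributes part of the centre difference to smell.

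**Working it through.** The plan gives no figure on this point to reproduce. The inputs are the counts and dates in the Results section, the pilot scores in the Introduction (8.9 against 9.9, a difference of 1.0 point) and the two-year event rates in the sample size section. Anything else is marked as assumed.

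**Enrolment**

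- Enrolled by April 2025: patients 32/64 = 50%, controls 9/64 = 14%.
- Still to come: patients 32/64 = 50%, controls 55/64 = 86%.
- Pace over about 23 months: patients 32/23 = 1.39 per month, controls 9/23 = 0.39 per month.
- Pace needed over the 20 months to December 2026: patients 32/20 = 1.6, controls 55/20 = 2.75, about seven times the past control rate.

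**Patients against controls**

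Suppose that scores obtained after April 2025, or at the newer centres, differ by *s* points for reasons unrelated to disease. Taking the share enrolled after April 2025 as the share exposed, the group difference moves by *s* × (55/64 − 32/64) = 0.359*s*.

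| Assumed *s* (points) | Movement of the difference (points) |
|---|---|
| 0.25 | 0.09 |
| 0.5 | 0.18 |
| 1.0 | 0.36 |

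The sign follows that of *s*. The article does not say which centres recruit controls, so the imbalance by centre could be smaller or larger than this imbalance by period.

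**Hyposmia against normosmia, overall survival**

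Expected deaths are 64 × (0.47 + 0.53)/2 = 32, so SE(log HR) is about 2/√32 = 0.354. Let *p1* and *p0* be the shares of hyposmic and normosmic patients at later centres, and *h* the hazard ratio of later centres against the first. With no smell effect, the hazard ratio for normosmia against hyposmia reads about (*p0h* + 1 − *p0*)/(*p1h* + 1 − *p1*). All centre inputs below are assumed.

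- 30% of patients at later centres, hyposmia 42% at the first centre and 58% later: *p1* = 0.174/0.468 = 0.372 and *p0* = 0.126/0.532 = 0.237. The ratio reads 0.96 for *h* = 1.3 and 0.94 for *h* = 1.5.
- 40% at later centres, hyposmia 40% and 60%: *p1* = 0.24/0.48 = 0.50 and *p0* = 0.16/0.52 = 0.308. The ratio reads 0.92 for *h* = 1.5 and 0.89 for *h* = 1.8.

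A simulation of 3,000 cohorts of 64 with 32 deaths gave medians of 0.95 (both cases with 30% at later centres), 0.925 and 0.889. With stratification by centre it gave 0.99 to 1.01, for 2 to 7% more variance.

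On the standard-error scale, |ln 0.95|/0.354 = 0.15, |ln 0.925|/0.354 = 0.22 and |ln 0.889|/0.354 = 0.33. The two-sided type I error becomes 5.2%, 5.6% and 6.3% instead of 5%. If the later centres have the lower hazard, the reading is mirrored, to about 1/0.95 = 1.05 up to 1/0.889 = 1.12. If smell groups are spread evenly over centres, there is no bias of this kind.

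**The case against.** The case against rests on four arguments.

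- **The test is standardised.** The section on the olfactory sense fixes forced choice among four options, the scoring, a period without food, drink, smoking or gum before testing, and non-disclosure of answers. Examiners and drift are not described. Some delay is natural when controls are matched to patients already enrolled. This stands: the shift of 0.25 to 1.0 points is an assumption and not an observation. What remains is that nothing in the matching rule would prevent such a shift from entering the comparison.
- **Case mix is already adjusted for.** MGMT, KPS, age and MRI findings are in both lists, and extent of resection is in one. This also stands. The simulation contained only smell and centre, so part of its centre effect would be removed by the planned model. Its precision cost is likewise not shown for a model with five or six covariates on about 32 deaths.
- **Centre handling is commonly left to an analysis plan, and that plan is not shown.** This is fair for the survival model, although the article does state its covariates explicitly. It does not cover where and when controls are enrolled.
- **A reader might infer more than the documents support.** One such inference is that the control lag also distorts the survival comparison. It cannot, because that comparison is made within patients. Another is that leaving out centre does bias the hazard ratio. That needs both smell status and survival to differ by centre, and the article shows neither. A third is that slow control recruitment leaves the patient-control comparison underpowered. That is a separate matter and would require the past pace to continue although centres are being added. It also depends on the difference chosen: the pilot's pre-treatment contrast was 9.9 − 8.2 = 1.7 points, and with an SD of 1.79 (implied by the pilot's p = 0.003 with 73 and 49 participants) even 17 controls, about 9 + 20 × 0.39, would give 93% power.

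**Conclusion.** The point holds for the patient-control comparison. Followed as written, the plan enrols 86% of controls but 50% of patients after April 2025, with at least two centres open and no matching on centre or time. The possible distortion is 0.09 to 0.36 points if the unrelated shift is 0.25 to 1.0 points. The pilot's 1.0-point difference is only a yardstick, since its controls were patients with other neurological diseases.

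For the primary survival comparison the point is minor. Centre is absent from both covariate lists and is a modest possible confounder. Under the assumed imbalances the displacement is at most about a third of a standard error, in either direction, and small beside the planned hazard ratio of 0.43.

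**What to change.** 1. Match the outstanding controls to patients on centre as well as age and gender.
2. For patients enrolled from now on, test the control close in time to the patient's first smell test. Do not impose a fixed window on patients already enrolled. With one control per patient, 32 − 9 = 23 of them still lack a control, and at 1.39 patients per month a 3-month window would reach back to only about 4. Controls would then be capped near 9 + 4 + 32 = 45, short of 64. Matching on centre remains possible for these patients.
3. Adjust the patient-control smell comparison for centre and test date. With 32 patients and 55 controls still to be enrolled, the two groups will overlap in time enough for this to be informative.
4. Stratify the Cox baseline hazard by centre (first centre against all others while those are small), at least as a pre-specified sensitivity analysis. Stratification adds no coefficient, which suits a model that already has 32/6 = 5.3 to 32/5 = 6.4 deaths per covariate.

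The cost is some analysis wording, one recruitment instruction, slightly harder control matching and a small loss of precision (2 to 7% more variance in the simplified simulation). Items 1 and 2 help only if they are in place before the remaining controls are enrolled.

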### Perspective

This prospective, multicenter observational study aims to clarify the prognostic significance and underlying mechanisms of olfactory dysfunction in newly diagnosed glioblastoma. Previous retrospective data have suggested an association between impaired olfaction and reduced survival in glioblastoma patients [12], but those findings were limited by potential confounders and lacked longitudinal follow-up. This study was designed to overcome these limitations by integrating rigorous stratification, serial olfactory testing, multimodal imaging, neurocognitive assessments, and molecular profiling.

The primary objective is to determine whether olfactory dysfunction independently predicts overall survival when accounting for established prognostic factors such as MGMT promoter methylation, KPS, age, and extent of resection. In parallel, two mechanistic hypotheses are tested: (1) direct tumor invasion of olfactory-related structures, and (2) neurotoxicity resulting from radiotherapy or chemotherapy. The aim is to prove that an olfactory dysfunction in glioblastoma is intrinsic to the disease and is not caused by radiochemotherapy or local tumor infiltration in the olfactory tract.

To assess structural involvement, high-resolution coronal T2-weighted MRI and DTI are employed to detect infiltration of primary and secondary olfactory regions. Metabolic activity in these areas is further evaluated using FET PET in clinically indicated cases. These imaging data are assessed independently by two neuroradiologists to ensure objective interpretation.

To investigate treatment-related neurotoxicity, olfactory function is longitudinally monitored over two years using both identification and threshold components of the Sniffin’ Sticks test. These data are complemented by repeated neurocognitive testing, and quality of life assessments, allowing for correlation between sensory decline, cognitive function, and psychosocial burden.

The study incorporates matched healthy controls to provide normative data and differentiate disease-specific patterns from age-related olfactory decline. Additionally, tumor genome sequencing and biobanking enable exploratory analyses of molecular correlates of hyposmia and clinical outcome.

Olfactory dysfunction has been implicated in various neurodegenerative disorders and, in oncology, as a marker of treatment-related neurotoxicity in other non-central nervous system malignancies [13, 16, 17]. In glioblastoma, additional mechanisms such as tumor spread via the RMS or microscopic invasion of olfactory structures may contribute [1, 4, 12]. This study is uniquely positioned to disentangle these processes through a multimodal, longitudinal approach.

While the study is ongoing and results are not yet available, its methodological rigor and comprehensive design position it to deliver conclusive insights into the prognostic, diagnostic, and pathophysiological relevance of olfactory dysfunction in glioblastoma. If our hypotheses are confirmed, olfactory testing could emerge as a simple, non-invasive tool to enhance risk stratification, monitor neurotoxicity, and guide personalized care strategies in neuro-oncology.

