Therefore, this prospective, multicenter study aims to determine whether olfactory dysfunction can serve as an independent prognostic marker for glioblastoma outcomes when controlling for known confounders and following patients longitudinally. The hypothesis is that the disturbance of olfactory function is intrinsically caused by the disease itself and not by external factors such as radiochemotherapy or tumor infiltration in structures of the olfactory tract.

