### Study procedures

#### Study visits

Study visits for glioblastoma patients will be scheduled as follows: screening (postoperative, once histology is available), baseline (as soon as MGMT promoter methylation status is determined, but before radiotherapy), visit 1 (4 ± 1 weeks after radiotherapy ends and before adjuvant chemotherapy begins), visit 2 (3 months ± 2 weeks after end of radiotherapy), visit 3 (6 months ± 2 weeks after end of radiotherapy), visit 4 (12 months ± 2 weeks after end of radiotherapy), and follow-up visits (every 6 months ± 2 weeks after visit 4, for a maximum of 2 years).

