#### MRI

All MRIs are used as part of clinical routine at the following points in time: Postoperative (24 h-72 h post surgery), before starting adjuvant chemotherapy (≈4 weeks post-radiotherapy), and approximately 3, 6, 12, 18, and 24 months after radiotherapy. The first post-radiotherapy MRI will be used to determine whether the tumor infiltrates the olfactory tract. A high-resolution coronal T2 sequence is required for this purpose. Two radiologists at independent centers will evaluate all MRIs. In contrast to the local radiologist, the reference radiologist is blinded to the patient's sex, name, and year of birth. Additionally, both radiologists are blinded to each other's assessment regarding olfactory tract infiltration on the MRI. In selected patients, a DTI (diffusion tensor imaging) sequence will be obtained for a more precise assessment of infiltration in olfactory regions.

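### The aim of proving that hyposmia is not caused by radiochemotherapy or tumour infiltration goes further than the design can show

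*Protocol article*

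**What the plan says.** The Introduction of the protocol article sets the hypothesis: "The hypothesis is that the disturbance of olfactory function is intrinsically caused by the disease itself and not by external factors", the external factors being radiochemotherapy and infiltration of olfactory structures. The Perspective section turns this into an aim: "The aim is to prove that an olfactory dysfunction in glioblastoma is intrinsic to the disease", adding that it "is not caused by radiochemotherapy or local tumor infiltration in the olfactory tract". The same section assigns structural involvement to MRI and DTI (with FET-PET where clinically indicated) and neurotoxicity to two years of serial olfactory tests. Healthy controls provide normative data.

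The parts of the design that bear on this aim are:

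- **First test.** The visit schedule begins with "screening (postoperative, once histology is available". The identification test at that visit assigns patients to hyposmia or normosmia. Baseline follows, still before radiotherapy. Patients have had no earlier chemotherapy (Table 2).
- **Infiltration rating.** "The first post-radiotherapy MRI will be used to determine whether the tumor infiltrates the olfactory tract" (MRI section).
- **Balancing.** Under Study cohort and Stratification, patients are stratified at visit 1 on factors that include MRI involvement, so that the two olfactory groups are balanced. Patients who cannot be placed leave the study.
- **Comparison group.** Healthy controls only.

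**The concern.** The aim is to establish the absence of two causes. That needs a design in which each cause, if present, would show itself, and an estimate precise enough to exclude an effect that matters. The two causes fare differently here, and the wording treats them alike.

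If the aim stands as written, failure to find an involvement effect could be reported as showing that hyposmia is intrinsic to glioblastoma. Yet the data might be unable to detect that effect, partly because of how the groups were formed. The primary survival objective is not affected. The headline mechanistic conclusion is.

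**Working it through.** **The plan's own figure.** The only size stated is for overall survival: "A hazard ratio (HR) of 0.43 for normosmia vs. hyposmia was used", 5% significance, 80% power, 64 patients and 64 controls. No margin or precision is stated for the mechanistic aim, so there is no figure to reproduce for it. (Two-sided, Schoenfeld's formula gives 4 × (1.96 + 0.84)² / (ln 0.43)² ≈ 44.1, rounded up to 45 events, or 90 patients at about 50% events. That does not reproduce 64, but it is a separate matter and nothing below depends on it.)

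**Time order.** Surgery, then screening and baseline tests, then radiochemotherapy, then visit 1 with the MRI used for the infiltration rating, then adjuvant chemotherapy.
- Hyposmia at screening cannot be due to later radiochemotherapy.
- It can be due to disease, surgery or perioperative effects, which are not separated.
- Decline after baseline can be due to treatment or progression. All patients belong to a treated population, and healthy controls have neither exposure.
- Baseline to visit 1 does not cover adjuvant chemotherapy, which falls in later visits.

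**Infiltration.**
- The Introduction and Perspective name microscopic infiltration or invasion as a possible cause. A negative MRI does not exclude it. DTI is done in selected patients and FET-PET only if clinically indicated.
- The rating is made later than the olfactory grouping it is meant to explain.
- If involvement were balanced exactly between hyposmia and normosmia, the odds ratio linking them among retained patients would be 1 whatever it was before. Partial balance pulls it part of the way.

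**SD of the identification score.** Back-calculated from the pilot results in the Introduction, assuming t-tests:
- 8.9 vs 9.9, 73 vs 49, p = 0.003 (t = 3.03): 1.0 / (3.03 × √(1/73 + 1/49)) ≈ 1.8.
- 8.2 vs 9.9, p = 0.001 (t = 3.45), taking n = 15 vs 49: 1.7 / (3.45 × √(1/15 + 1/49)) ≈ 1.7.

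I use 1.8 and show 2 as an alternative.

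**Involved vs uninvolved, 64 patients.** Half-width = 2.00 × SD × √(1/n₁ + 1/n₂). The split is assumed, since the article gives none. Equivalence power is for an assumed 1-point margin: 2Φ(1/SE − 1.645) − 1.

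| Split | Half-width, SD 1.8 | Equivalence power |
|---|---|---|
| 32/32 | 0.90 | 44% |
| 20/44 | 0.97 | 32% |
| 13/51 | 1.12 | 11% |

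At SD 2 and 20/44: 1.96 × 2 × √(1/20 + 1/44) = 1.06. As a difference in hyposmia proportion (47% overall), the half-width is 24 to 30 percentage points. About 56 patients per group would give 80% equivalence power: 2 × (1.8 × (1.645 + 1.282))² = 55.5.

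**Mean change, baseline to visit 1.** SD of change = 1.8 × √(2(1 − r)); half-width = t × SD of change / √n.

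| r (assumed) | SD of change | 64 pairs | 32 pairs |
|---|---|---|---|
| 0.3 | 2.13 | 0.53 | 0.77 |
| 0.5 | 1.80 | 0.45 | 0.65 |
| 0.7 | 1.39 | 0.35 | 0.50 |

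A change centred on zero would exclude a 1-point mean decline in every cell. With an SD of change of 3.0 the half-width is 0.75 with 64 pairs and 1.08 with 32.

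**Later visits.** Taking the pilot medians as exponential, 24-month survival is 0.5^(24/20.9) = 0.451 for hyposmia and 0.5^(24/40.6) = 0.664 for normosmia. From the pilot split (34/73 = 0.466), the hyposmic share among survivors is 0.466 × 0.451 / (0.466 × 0.451 + 0.534 × 0.664) = 0.37. About 0.565 × 64 = 36 patients remain. A visit mean could rise with no individual improving.

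**The case against.** The strongest reply is that the article does more than the criticism allows. It gives each mechanism its own data. It fixes olfactory status before radiotherapy in patients without earlier chemotherapy, it speaks of hypotheses being tested, and its secondary analyses may be set out in a plan not shown. Much of this stands, and it rules out several stronger readings.

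- *The survival model is meant to show the mechanism.* A reader might infer this because "A Cox proportional hazards regression model will be used to describe the event, overall survival" is the only model described. The article does not assign the mechanistic question to it, and the absence of a stated model for the serial tests is no fault in a condensed article.
- *The design says nothing about radiochemotherapy without an untreated group.* Time order already excludes it for hyposmia present at screening. The missing group matters only for later decline.
- *A null before-after result would be too imprecise.* The paired figures show otherwise for the mean change to visit 1. Imprecision returns only with a larger SD, a smaller margin, heavy attrition or decline confined to a subgroup.
- *A null involvement result would leave infiltration able to explain the whole pilot gap of 1.0 point.* It would not. With 20 of 64 involved, a 1.06-point effect moves the patient mean by 0.3125 × 1.06 = 0.33 point. Explaining 1.0 point would need 1.0 / 0.3125 = 3.2 points.
- *Non-significance will be read as proof.* No section states that rule. Nor does any section plan to compare raw visit means, so the survivorship figure is a caution for reporting only.

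What the reply does not meet is the stated aim itself, the postoperative first test, the limit of MRI for microscopic invasion, and the balancing with exclusions.

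**Conclusion.** The point holds in a limited form. The aim of proving that olfactory dysfunction is intrinsic, and due to neither radiochemotherapy nor infiltration, is more than this design can show.

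- **Radiochemotherapy:** excluded by time order as a cause of hyposmia at screening. Surgery remains inseparable from disease, and later decline from progression. A 1-point mean decline to visit 1 can be excluded.
- **Infiltration:** the weaker side. Microscopic invasion is not observable on MRI, the group balancing weakens the association by design, and the contrast carries a half-width of about 0.9 to 1.1 points. Under the two more even splits, a result centred exactly on zero would only just exclude 1 point; under 13/51 it would not.

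The figures rest on an SD of 1.8 derived from pilot p values, assumed splits and correlations, an assumed 1-point margin, and 64 patients contributing. This study averages scores over nostrils, so its SD may differ from the pilot's. The article does not say how closely balance is enforced or how many patients will be excluded. The effect of the balancing is therefore certain in direction but not in size.

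**What to change.** Replace the proof wording in the Introduction and Perspective with three estimates, each with a 95% CI:

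1. Olfaction at the pre-radiotherapy baseline visit, patients without visible involvement against matched controls.
2. Within-patient change from baseline to visit 1, stating the largest decline the interval does not exclude. Start from the baseline visit, because the screening score forms the groups and change measured from it would carry regression to the mean.
3. Involved against uninvolved patients at baseline, among all enrolled patients before the visit 1 balancing exclusion. Note that involvement is rated on the post-radiotherapy MRI, so patients without that scan have no rating.

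Show later visits against the same survivors' baseline values. Say that a non-significant test is not evidence of no effect, and that surgery cannot be separated from disease. Limit the conclusion to hyposmia being present before radiotherapy and not fully explained by visible involvement, if the estimates bear that out.

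The cost is a less absolute conclusion and a little more analysis of data already being collected. Baseline data from patients excluded at visit 1 must be kept for the third estimate. Enrolment is planned to December 2026, so the change can be made before results are known.
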